#### Dosimetry

Cumulative dosimetry will be determined as formulated above in table 2. Comparison of cumulative doses between the treatment groups will be done by calculating the difference in mean dose with its 95% CI.

#### Quality of life (QoL)

Continuous sum-scores of the QoL questionnaires will be compared by calculating differences in QoL and their 95% CIs. Changes in QoL will also be compared across groups.

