In an earlier study we listed all known publications and studies on home UVB phototherapy, and conducted a survey among dermatologists [14]. We found that in the Netherlands home UVB is currently prescribed to approximately 5% of the UVB-treated patients, with some dermatologists prescribing it in 100% of the cases. We also demonstrated that there is no firm evidence that would either support or dissuade from prescribing home UVB phototherapy. Glaringly absent is any randomised research in this area. This lack of research has resulted in ongoing discussions and the dissemination of personal, non-evidence based opinions, especially with regard to issues like effectiveness, side effects and cost [14]. Thus, in general, home UVB phototherapy remains a debated treatment. We concluded that only randomised research on home UVB phototherapy as compared to UVB treatment in an outpatient setting could resolve the issue [14].

In this paper, we describe a randomised pragmatic trial that we are currently conducting, a national trial on home UVB phototherapy for psoriasis. The Dutch acronym for this trial is PLUTO (Psoriasis: Landelijk UVB Thuisbelichtings Onderzoek). The trial is designed to evaluate the impact of home UVB phototherapy versus conventional outpatient UVB phototherapy on effectiveness, quality of life and cost-effectiveness. The focus is on narrowband UVB treatment (TL-01 lamps). The study tests the hypothesis that home UVB phototherapy is as effective as outpatient UVB phototherapy. We further expect a better quality of life when patients are treated at home, and we hypothesize that home treatment will have similar or reduced total costs. This article presents the design of this trial.

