## Methods

### Objective

The aim of this study is to compare home UVB (TL-01) phototherapy with the current outpatient UVB (TL-01) phototherapy for patients with psoriasis. This objective was specified by the following research questions. Compared to outpatient UVB phototherapy:

1. Is home UVB phototherapy for patients with psoriasis equally effective?

2. Does home UVB phototherapy yield a better quality of life?

3. Are costs for home UVB phototherapy higher, lower or similar?

4. Is home UVB phototherapy cost-effective?

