#### Quality of life (QoL)

To assess quality of life we used one disease-specific questionnaire and several universal questionnaires. The standard questionnaires that were used were:

• Psoriasis Disability Index (PDI) [26,27]

• Short Form-36 (SF-36) [28,29], and

• EuroQol (EQ-5D) [30,31]

The PDI is a short questionnaire consisting of 15 questions regarding disability due to psoriasis. Answers are recorded on a seven point linear scale where '1' indicates no disability and '7' indicates maximum disability. Therefore the maximum potential PDI score is 105, with a minimum of 15 [27]. One of the generic QoL questionnaires used in the study is the SF-36, a 36-item questionnaire yielding a profile of 8 dimensions. All dimensions range in score from 0 to 100, with higher scores indicating a higher level of health status. By adding weighted combinations, the 8 scales can be combined into a physical and a mental component summary score. The EQ-5D is also a generic quality of life questionnaire. It was developed to assess the impact of a disease in terms of multi-attribute value judgements yielding one overall value judgement, a so-called utility score ranging between 0 (dead) and 1 (optimal health) [30,31]. When utility scores are plotted against time, the Area Under the Curve (AUC) reflects the Quality Adjusted Life time usually expressed in Years (QALY's). Thus QALY's will be calculated as follows: utility scores from two timepoints will be linearly interpolated (i.e. summed and devided by two). This outcome will be multiplied by the time difference. This procedure will be repeated for all parts of the curve, and the outcomes of all parts of the curve will be summed and ultimately yield an estimate of the entire AUC. In this way QALY's will be calculated for all patients, and a mean and standard error of the mean (SEM) will be determined.

Besides these standard questionnaires, we designed a brief "Burden of treatment" (BOT) questionnaire with 4 questions on the perceived burden of the UVB treatment (especially the specific burden of the treatment method and the burden of the time lost to treatment), and we developed a questionnaire on patient satisfaction. The patient satisfaction questionnaire asked about:

• waiting times,

• perceived improvement of the psoriasis lesions,

• satisfaction with the treatment as a whole,

• satisfaction with the final treatment result,

• satisfaction with the rate of improvement,

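### Each quality-of-life score is compared between arms twice, raw and as change, where one prespecified baseline-adjusted difference would be at least as precise and could not contradict itself

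*Protocol article*

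**What the plan says.** Research question 2 in the Objective section asks: "Does home UVB phototherapy yield a better quality of life". The Background gives the expected answer: "We further expect a better quality of life when patients are treated at home".

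The outcome section on QoL names three standard instruments:

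- The PDI gives one total: "the maximum potential PDI score is 105, with a minimum of 15".
- The SF-36 is "a 36-item questionnaire yielding a profile of 8 dimensions", and "the 8 scales can be combined into a physical and a mental component summary score".
- The EQ-5D is described as "yielding one overall value judgement, a so-called utility score".

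Under Measurement planning, questionnaires go out at about 23 irradiations and at the end of therapy (or 46 irradiations). The Cost-effectiveness section confirms that no QoL questionnaire follows after irradiation stops.

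The QoL part of Statistical analysis is two sentences: "Continuous sum-scores of the QoL questionnaires will be compared by calculating differences in QoL and their 95% CIs", and then "Changes in QoL will also be compared across groups". The opening paragraph of Statistical analysis adds adjustment in a multivariable model, but only where baseline differences look apparent. The Randomisation procedure section says that allocation was by minimisation on recruiting hospital and previous UV phototherapy.

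**The concern.** The plan fixes two unadjusted answers to the same question for every score at every visit: the difference in the score, and the difference in its change. It does not say which one is to be read. If the arms differ at baseline by chance, the two move in opposite directions away from the true effect. One may then exclude zero while the other does not.

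Both contrasts also give up precision that costs nothing to recover. A comparison of changes needs a baseline score, so the covariate is available. The minimisation factors are known for every patient but are not in the stated comparison.

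At stake are a clear answer to one of the trial's four research questions and some width of its confidence intervals. Patients are not blinded, the scores are self-reported and a benefit at home is expected, so it matters that the estimate to be reported is fixed beforehand.

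**Working it through.** The article gives no QoL sample size, power or error rate to reproduce. Its 90 per group concerns treatment response only and does not bear on this point.

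**Inputs.** Table 3 gives 50 + 48 = 98 patients per arm. I take change to mean change from baseline and assume equal variance at baseline and follow-up and complete data. The baseline-to-follow-up correlation r is assumed.

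**1. How far the two contrasts can differ.** Let the true effect be δ and the chance baseline difference d, both in SD units. Given d, the expected estimates are:

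- raw difference: δ + r·d
- difference in change: δ − (1 − r)·d
- baseline-adjusted difference: δ

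The first two differ by r·d + (1 − r)·d = d. Under simple randomisation the standard error of d is √(2/98) = 0.143 SD, so 95% of trials have d within ±1.96 × 0.143 = ±0.28 SD.

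The correlation between the raw and change estimates is √((1 − r)/2): 0.59 at r = 0.3, 0.50 at r = 0.5 and 0.39 at r = 0.7. For one score at one visit with no true effect, the chance that at least one of the two intervals favours home is 0.025 + 0.025 − P(both). From the bivariate normal, P(both) is 0.006, 0.005 and 0.003, which gives 4.4%, 4.5% and 4.7%, against 2.5% for a single contrast.

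**2. Precision.** Variances relative to the raw difference are 1 (raw), 2(1 − r) (change) and 1 − r² (adjusted). The gain is 1 − (1 − r²)/min(1, 2(1 − r)).

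| r | raw | change | adjusted | gain over the better of the two |
|---|---|---|---|---|
| 0.3 | 1 | 1.40 | 0.91 | 9% |
| 0.5 | 1 | 1.00 | 0.75 | 25% |
| 0.6 | 1 | 0.80 | 0.64 | 20% |
| 0.7 | 1 | 0.60 | 0.51 | 15% |
| 0.8 | 1 | 0.40 | 0.36 | 10% |

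The gain peaks at r = 0.5. Adjustment is never worse than either planned contrast.

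**3. Number of scores.** The narrow reading of sum-scores has 4 overall scores: PDI 1, SF-36 summaries 2, EQ-5D 1. The widest has 1 + 8 + 2 + 1 = 12. At two visits with one contrast each, that is 8 to 24 intervals. I simulated correlated normal statistics under no difference, with an assumed visit correlation of 0.7. The chance that at least one 95% CI favours home is:

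| between-score correlation (assumed) | 4 scores | 12 scores |
|---|---|---|
| 0.3 | 14% | 30% |
| 0.5 | 12% | 24% |
| 0.7 | 10% | 18% |

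With both contrasts kept (16 to 48 intervals), the range is about 19% to 51%.

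**The case against.** The strongest reply is that this is a condensed article. Which QoL score leads, and how multiplicity is handled, are commonly left to the analysis plan, and nothing in the article rules out a ranking there. That stands for the choice of a lead score, which is why it is only an option below. It does not cover the two contrasts, which the article states outright.

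A second reply is that adjustment is already foreseen. It is, but only when differences look apparent. That trigger is undefined and applied after the data are seen. When it fires it adds a third estimate, and when it does not the precision is still lost.

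Three stronger readings are tempting, and the article does not support them:

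- A reader might infer that baseline scores go unused. The change contrast uses them, only less efficiently than adjustment.
- A reader might infer at least 12 scores and 48 intervals, any one of which would establish a benefit. Twelve is the widest reading, and the SF-36 summaries are built from the eight scales already counted. The plan is framed as estimation and has no rule that one favourable interval suffices.
- A reader might infer that the PDI must decide. Nothing ranks it above the others, and the EQ-5D carries the QALY analysis. The trial is sized on treatment response, not on QoL.

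**Conclusion.** The point holds for the choice of contrast. The article fixes two unadjusted comparisons per score where one adjusted comparison is at least as precise and leaves no choice between answers. The variance reduction is about 9% to 25% against the better of the two for r between 0.3 and 0.8, under assumed correlations and equal variances. It is 25% only at r = 0.5.

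The absence of a lead score is a secondary matter. The chance of at least one interval favouring home under no difference is about 10% to 30% with one contrast per score. That range rests on assumed score and visit correlations and on whether 4 or 12 scores are counted. It is a reason to consider naming a lead score, not evidence that the plan would make a false claim.

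**What to change.** For each QoL score and time point, replace the two contrasts by one prespecified between-arm difference with 95% CI, adjusted for:

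- the baseline value of that score;
- previous UV therapy;
- recruiting hospital, with small centres pooled or hospital as a random effect (Table 3 has 14 hospitals, the smallest with 3 and 4 patients).

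Make this adjustment unconditional for QoL, so that it does not depend on whether a baseline imbalance is noticed. Raw means and changes can still be shown descriptively.

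Optionally, name in advance one score and time point to answer research question 2, for example the PDI at the end of therapy or 46 irradiations, and treat the others as supportive.

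The cost is analysis wording and slightly more modelling, with no new data. If a lead score is named, the other scales can no longer support a claim of better quality of life on their own.

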#### Costs

Both costs as reimbursed by the health insurance companies and actual costs as calculated by including all expenses (direct and indirect) will be compared for the two treatments as difference in cost with a 95% CI. The uncertainty associated with the point estimates will be evaluated using bootstrapping [35].

#### Cost-effectiveness

Initially the trial estimate of the incremental cost per additional patient with successful outcome will be assessed. Similarly, the cost per QALY gained will be estimated. To assess uncertainty with regard to incremental cost-effectiveness a standard bootstrap technique will be applied [35]. The trial data will be randomly sampled with replacement from the original dataset 1000 times. For each bootstrap sample the incremental costs and effects will be calculated and plotted (costs on the y-axis and effects on the x-axis). Thus an integrated presentation of the mutually dependent cost and effect differences is obtained that may be interpreted as a direct reflection of the uncertainty, i.e. a two dimensial dispersion, with regard to the incremental cost-effectiveness ratio. Using this so-called CEA Plane (Cost-effectiveness Analysis Plane), an inference regarding the likelihood of one treatment being more cost-effective than the other can be made [36].

#### Other data

These include concomitant use of medication, data on patient satisfaction and on the burden of both treatments. These data will also be compared across groups and be presented as differences with 95% CIs.

## Results

Recruitment of patients was stopped after 2 years and 2 1/2 months. Initially 252 possible participants were recruited by the participating hospitals. Of these 252 patients, 56 were excluded from starting the trial for a variety of reasons. Thirty-three (33) patients had a clear preference for either home or hospital-based therapy and refused to submit to being randomised. Another 11 patients did not want to participate in a study, 6 patients did not fulfill the inclusion criteria or met one of the exclusion criteria, 2 had already started UVB therapy, 2 persons decided not to be treated with UVB, and 2 patients were excluded for other practical reasons.

Thus, in total 196 patients (252–56) were included in the study. A consecutive sample of 105 patients was followed for 12 months after the end of the treatment in order to gain sufficient data about the costs incurred after the treatment. Randomisation according to the minimisation method [19] was successful. The two factors accounted for, their levels and the number of assigned therapies are shown in table 3.

**Table 3 T3:** Results of the randomisation procedure.

		**Number of patients**		
**Factor**	**Level**	**Hospital**	**Home**	**Total**
**Hospital**	UMC Utrecht	24	25	49
	Hilversum Hospital	14	15	29
	Academic Hospital Maastricht	9	9	18
	Diakonessen Hospital Utrecht	9	8	17
	Meander Hospital Amersfoort	7	8	15
	Groene Hart Hospital Gouda	6	5	11
	AMC Amsterdam	5	5	10
	Erasmus MC Rotterdam	5	4	9
	VUmc Amsterdam	4	5	9
	Gelre Hospital Apeldoorn	5	3	8
	Diakonessen Hospital Zeist	3	4	7
	Reinier de Graaf Hospital Delft/Voorburg	4	3	7
	AntoniusMesosGroup Hospitals Nieuwegein/Utrecht	2	2	4
	Lucas Andreas Hospital Amsterdam	1	2	3

**Previous UV phototherapy**	Yes	50	50	100
	No	48	48	96

Stratified randomisation, in particular the minimisation method described by Pocock [19] was used, which took into account (1) the recruiting hospital, and (2) possible previous experience of the patient with UV therapy. This table shows the results of the treatment assignment by the two factors for 196 patients.

The therapy took place according to randomisation for 184 patients. Five (5) patients switched therapy (protocol violators), of which four patients switched to home UVB phototherapy. Another seven (7) patients never started therapy. Of those seven patients, four (4) had their lesions improve during the waiting period before treatment could be started and did not need UVB treatment after all (three of them were randomised to the group receiving home UVB treatment). The other three (3) that did not receive therapy withdrew respectively because of agoraphobia, not wanting to participate in the study, and not wanting any treatment during pregnancy. Two of them were assigned to have outpatient phototherapy.

## Discussion

This article presents the design of the first randomised controlled trial of home UVB phototherapy for psoriasis. The design of this trial was 'pragmatic', which means that we did not adapt daily practice to conform to a specific protocol: the two treatments were compared under the conditions in which they would be applied in daily practice [15]. In contrast to a pragmatic trial, an 'explanatory' trial studies treatments under controlled idealised or equalised conditions, preferably by means of a double-blind placebo-controlled study design and a rigid research protocol [15]. Thus, explanatory trials aim at providing information on the effects of a single difference in treatment, while a pragmatic trial compares two treatment strategies as a whole [15]. Consequently, in a pragmatic trial the treatments will be carried out just as they would have been without the trial, and therefore the advantage of a pragmatic design is the assurance that the results can easily be generalised to the target population. As a result, this trial will make a valuable and important contribution to the evidence base for the use of home UVB phototherapy for patients with psoriasis. It will produce a solid estimate of the effectiveness of home UVB treatment compared to UVB phototherapy in an outpatient setting.

Of the five previously conducted studies on home UVB treatment, only two compare two groups of patients [14]. Our study addresses two weaknesses encountered in those earlier studies. First of all, our trial has a parallel group design in order to compare the two treatments during the same seasons of the year. Secondly, to obtain two similar groups of patients and thus prevent selection bias, assignment of treatments is by randomisation. As such, this study is the first to perform a parallel group randomised comparison of home UVB phototherapy with UVB treatment in an outpatient setting.

Another strength of the study is that it is designed to compare the two treatments as they are carried out in daily practise (pragmatic design), guaranteeing a good generalisability of the results. A further substantial difference with other trials in this field is that in addition to the effectiveness of the two therapies, the impact of each treatment on quality of life and on its associated costs is assessed. A cost-effectiveness analysis will be conducted to investigate the aspects of expense and effectiveness together. The trial will also provide information about patient satisfaction, travel time, side effects, cumulative dosimetry, concomitant use of medication, waiting periods and total treatment duration. The manner in which data collection was planned throughout the trial ensures that both groups can be compared during the treatment period without important differences in the number of irradiations. During the follow-up the measurements are all comparable with regard to the time interval since the last irradiation.

There are however also some weak points which bear discussion. For instance, because the measurement planning does not use fixed time points starting from inclusion, for most patients the outcome at 12 months after inclusion (used to calculate cost-effectiveness) will have to be interpolated from the two adjacent measurements. These two adjacent measurements are only two months apart, thus providing a solid basis for interpolation. Also, the EQ-5D questionnaire was only administered until the end of the treatment and not during the remaining follow-up period, making direct calculation of QALY's for this period impossible. We will have to rely on extrapolation from the treatment period. Another issue for discussion is that during the trial it was impossible to keep a record of all patients with psoriasis who were prescribed TL-01 UVB treatment but who were nòt referred to the central coordination centre. We therefore do not know the reasons for non-referral.

Overall, we feel that this trial has many benefits and will prove to be a very valuable addition to the current literature in the field. It is the first trial to compare these two commonly used treatments directly in a randomised parallel group design. Moreover, the study design allows for more than one objective. Besides clinical effectiveness, it also evaluates quality of life and cost-effectiveness. Being a pragmatic trial, it will be easy to generalise the results of this study to the target population. With 196 participants, the study is adequately powered to detect a 15% reduction in effectiveness, and the other outcome parameters can also be determined adequately. The results of this study will be available in 2006.

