### Sample size

The sample size could not be calculated on the basis of presumed differences in effectiveness as there is no clear data available on the possible differences in treatment effects. However, based on the data available from a 1993 pilot study [16] and recent experience with home UVB phototherapy, we in fact expected the effectiveness of both therapies to be similar. The sample size was therefore calculated in accordance with a negative trial approach [17]. We considered a 50% or greater improvement in the psoriasis severity from baseline to be a relevant clinical response. A systematic review by Spuls et al. indicates that approximately 85% of the patients treated with UVB show at least a 50% improvement in their psoriasis [18]. Thus, with N = 90 per per treatment group and at α = 0.05 and β = 0.20 (power 80%), we would be able to show a difference in effectiveness of 15% or more; i.e., a reduction in effectiveness from 85% to 70% or less should be distinguishable. To allow for missing data and losses to follow-up (i.e. withdrawals, incomplete case register forms) we aimed at 100 patients per group, 200 in total. To obtain accurate estimates of the cumulative costs of UVB treatment a consecutive sample of 100 patients (50 per group) was considered to be sufficient, because little variation was expected in treatment duration, number of UVB irradiations, and use of concomitant medication.

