**Figure 1 F1:**
[figure not shown]
**Timetable**. Schematic representation of successive time points for data collection, reported for all outcome measures and questionnaires. * 23 irradiations: outcome measurement was planned at approximately 23 irradiations, with a minimum of 20 and a maximum of 26 irradiations. ** End of therapy: measurement was planned at the end of the treatment. When more than 46 irradiations were needed, measurement was planned at 46 irradiations. *** Follow-up: Starting at the end of the therapy (or at the 46^th ^irradiation, see **), follow-up measurements were planned every 2 months, for up to 1 year after the last irradiation.

Immediately after this first visit, patients were randomised using the baseline data (information on the recruiting hospital and any previous experience of the patient with UV therapy were used to determine the randomisation strata). Both patient and attending dermatologist were informed about the type of treatment assigned, and the treatment was started accordingly. When (sometimes after a waiting period) the therapy was started, the patients did a SAPASI-assessment and began using the study diary. At approximately 23 (20–26) UVB treatments ànd at the end of the therapy (or 46 treatments) the patients received a series of questionnaires at home. Visits to the previously mentioned research nurse were scheduled for the same time points. Throughout the whole trial, the independent research nurse was not informed about the randomisation results and therefore remained blinded.

For all UVB therapies lasting longer than 46 treatments, a cutoff point of maximally 46 treatments was used to establish effectiveness. The choice of 46 as the maximum number of treatments was derived from unpublished data from the home care organisations about the treatment duration of their patients.

At the end of the therapy (or 46 treatments), 105 patients were followed for 12 more months to monitor long term effectiveness and cost. The patients received a short questionnaire at home every 2 months and returned this questionnaire by mail. At the end of the follow-up, information on medication use during the trial period was retrieved retrospectively for each patient from his/her pharmacist.

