#### Effectiveness

Assessment of effectiveness of both UVB treatments will take place through calculation of the PASI and SAPASI-scores for both treatment modalities at regular points in time, and subsequently calculating differences in (SA)PASI scores over time. Possible differences in effectiveness between the two therapies will be established through comparison of differences in (SA)PASI scores inclusive of 95% CIs. The side effects of the therapy were reported for each irradiation as being present ("yes") or not being present ("no"). For each type of side effect the answers will be compared on a group level and presented with their 95% CIs.

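### The adequacy statement rests on 196 participants, but long-term and 12-month effectiveness rest on 105 sized for costs, and the 15% equality rule has no confidence limit

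*Protocol article*

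**What the plan says.** The Sample size section defines response as at least 50% improvement from baseline, takes 85% as the expected rate, and uses a negative-trial calculation with 90 per group: "a reduction in effectiveness from 85% to 70% or less should be distinguishable". The target was 100 per group to allow for losses, and 196 patients were included.

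The same section sizes a smaller sample for cumulative costs: "a consecutive sample of 100 patients (50 per group) was considered to be sufficient, because little variation was expected in treatment duration". The Results again give post-treatment costs as the reason for following 105 patients. Measurement planning, however, gives the follow-up a second purpose: "105 patients were followed for 12 more months to monitor long term effectiveness and cost".

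The economic evaluation has a horizon of 12 months from inclusion. The Discussion says that, for most patients, "the outcome at 12 months after inclusion (used to calculate cost-effectiveness) will have to be interpolated from the two adjacent measurements", and those measurements are the two-monthly follow-up questionnaires.

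The Cost-effectiveness subsection under Outcome assessment holds the only equality rule. A difference in effectiveness below 15% counts as equal effectiveness, and the evaluation is then limited to cost minimisation. The rule does not say whether it refers to the point estimate or a confidence limit, or to which time point it applies. For scores, the Statistical analysis section says: "Possible differences in effectiveness between the two therapies will be established through comparison of differences in (SA)PASI scores inclusive of 95% CIs".

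The Discussion then states: "With 196 participants, the study is adequately powered to detect a 15% reduction in effectiveness, and the other outcome parameters can also be determined adequately".

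**The concern.** The adequacy statement carries the size of the whole trial over to outcomes measured in about half of it. No section justifies 105 patients for showing that home treatment is as effective in the long term, although long-term effectiveness is a declared purpose of the follow-up.

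This bears on the economic conclusion. The equality rule decides whether effects are compared at all, or only costs. If it is applied at 12 months to a point estimate from about 52 patients per arm, a real loss of the size the trial calls relevant could be labelled equal and would then drop out of the economic comparison. A reader who relies on the adequacy statement would not see this.

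**Working it through.** **Inputs from the article.** Response 85%; limit 15 points; 90 per group; power 80%; α = 0.05; 196 included; 105 followed.

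**Assumptions.** The 105 split 52/53 (the split is not stated). There is no attrition. A severity score allowing the 50% criterion is collected at follow-up (the timetable figure is not shown). Long-term response lies between 50% and 85%, because relapse is not quantified.

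**Step 1: the article's own figure.** For excluding a loss of 0.15 when both arms respond at 85%, with one-sided α = 0.025:

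n = 2 × 0.85 × 0.15 × (1.96 + 0.8416)² / 0.15² = 0.255 × 7.849 / 0.0225 ≈ 89 per group.

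This agrees with the stated 90 and with a negative-trial approach. The same framework is therefore used below.

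**Step 2: the same criterion with 105 patients.**

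SE = √[p(1 − p)(1/n₁ + 1/n₂)]; power = Φ(0.15/SE − 1.96); half-width = 1.96 × SE.

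| Patients per arm | Response in both arms | SE | Half-width (points) | Power to exclude a 15-point loss |
|---|---|---|---|---|
| 90/90 | 85% | 0.0532 | 10.4 | 80% |
| 52/53 | 85% | 0.0697 | 13.7 | 58% |
| 52/53 | 70% | 0.0894 | 17.5 | 39% |
| 52/53 | 50% | 0.0976 | 19.1 | 34% |

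For the second row: 0.15/0.0697 − 1.96 = 0.19, and Φ(0.19) ≈ 0.58. In the last two rows the half-width exceeds 15 points, so an observed difference of exactly zero would not exclude the limit.

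**Step 3: does the 12-month outcome fall in the follow-up period?** Outpatient irradiation is given 2 to 3 times a week, and effectiveness measurement stops at 46 irradiations. That takes 46/3 ≈ 15 to 46/2 = 23 weeks, and less at the home frequency of 3 to 4 a week. Follow-up counts from the end of therapy or the 46th irradiation. Unless waiting or interruptions are very long, 12 months after inclusion therefore lies in follow-up, where only the 105 contribute.

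**Step 4: the equality rule.** Read as a point estimate, the rule declares equality when the observed loss is below 15 points. If the true loss is 15 points, the estimate is centred at 15 and falls below it with probability about 0.5. This holds at any sample size, so the error at the limit is about 50% with 105 patients and with 196.

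**The case against.** The strongest reply is that the adequacy sentence does not mention follow-up. Quality of life, side effects, dosimetry, burden and satisfaction do not depend on the 105, and the subset has its own justification for costs. That is fair, and the main end-of-therapy comparison is untouched. But the sentence covers the other outcomes without exception and cites 196, while long-term effectiveness is a stated purpose of a follow-up in 105. The mismatch stands.

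Three stronger readings are tempting, and the article does not support them.

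- *An interval including zero will be taken as long-term equality.* The article nowhere says so. It plans estimates with 95% confidence intervals, and its one equality rule uses 15%.
- *The follow-up is inadequate because a 0.5-SD difference in score is missed about 28% of the time.* The arithmetic is right for 52 against 53 at two-sided 5%, but 0.5 SD is not in the article. The miss rate runs from about 66% at 0.3 SD to 5% at 0.7 SD. It follows from the sample size, not from the absence of a score margin.
- *Time points will be analysed separately, and a six-visit mean SAPASI should replace them.* The article does not exclude a longitudinal model, and that choice commonly belongs to the analysis plan. A six-visit mean also changes the question. If a 0.5-SD loss appeared only in the last three visits, the mean would miss it 62% to 72% of the time at assumed within-patient correlations of 0.5 to 0.8.

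It is also true that the 15% rule may be meant for the end of therapy. The article does not say. It places the rule beside a 12-month horizon, and Step 4 applies at either time point.

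**Conclusion.** The point holds as a mismatch between a claim and the data behind it, together with an equality rule that lacks a confidence limit. On the trial's own responder scale, the followed patients give about 58% power to exclude a 15-point loss if 85% respond in both arms. They give 34% to 39% if long-term response is 50% to 70%. With 90 per arm at 85% it is 80%.

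The 58% depends on the assumed even split and full retention, and attrition would lower it. The 34% to 39% also depends on the assumed long-term response. The 50% error of the point-estimate reading depends on neither. The documents do not show that a wrong conclusion will be drawn. They show that the follow-up cannot carry the adequacy claimed for it, and that nothing in the stated rule guards against over-reading it.

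**What to change.** 1. **Discussion.** Limit the adequacy statement to the end-of-therapy outcome. State the precision for the 105 followed patients: the actual split by arm, the expected half-width on the responder scale, and the power to exclude a 15-point loss over a range of long-term response rates.
2. **Cost-effectiveness (Outcome assessment) and Effectiveness (Statistical analysis).** Conclude equal effectiveness at follow-up or at 12 months, and restrict the evaluation to cost minimisation, only if the 95% confidence limit for the responder difference excludes a 15-point loss with home UVB. Otherwise report the estimate and interval without an equality claim, and carry out the full cost-effectiveness analysis with the bootstrap already planned.

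This needs wording changes only and no new data. The cost is a less favourable statement about follow-up and a real chance of an inconclusive long-term result. Even with truly equal response of 85%, the limit would fail to exclude 15 points about 42% of the time (100 − 58), and 61% to 66% of the time if response is 50% to 70%.
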